# The effect of supplemental oxygen on perioperative brain natriuretic peptide concentration in cardiac risk patients – a protocol for a prosprective randomized clinical trial

**DOI:** 10.1186/s13063-020-04336-9

**Published:** 2020-05-12

## Abstract

**Background:**

Elevated postoperative *N*-terminal pro-B-type natriuretic peptide (NT-proBNP) concentrations are predictive for cardiac adverse events in noncardiac surgery. Studies indicate that supplemental oxygen decreases sympathetic nerve activity and might, therefore, improve cardiovascular function. Thus, we will test the effect of perioperative supplemental oxygen administration on NT-proBNP release after surgery.

**Methods/design:**

We will conduct a single-center, double-blinded, randomized trial at the Medical University of Vienna, including 260 patients with increased cardiac risk factors undergoing moderate- to high-risk noncardiac surgery. Patients will be randomly assigned to receive 80% versus 30% oxygen during surgery and for 2 h postoperatively. The primary outcome will be the difference in maximum NT-proBNP release after surgery.

As secondary outcomes we will assess the effect of supplemental oxygen on postoperative maximum troponin T concentration, oxidation-reduction potential, von Willebrand factor concentration and perioperative fluid requirements. We will perform outcome measurements 2 h after surgery, on postoperative day 1 and on postoperative day 3. The NT-proBNP concentration and the oxidation-reduction potential will also be measured within 72 h before discharge.

**Discussion:**

Our trial should determine whether perioperative supplemental oxygen administration will reduce the postoperative release of NT-proBNP in patients with preoperative increased cardiovascular risk factors undergoing noncardiac surgery.

**Trial registration:**

ClinicalTrials.gov, ID: NCT03366857. Registered on 8th December 2017.

## Background

Major cardiovascular complications occur in about 3% of all patients undergoing noncardiac surgery [1, 2]. In patients over the age of 45 years the risk of developing postoperative complications is even higher [2].

As supplemental oxygen has no effect on the incidence of surgical site infections, it is reasonable to question the effect of hyperoxia on other organ systems [3–6]. The systemic effect of perioperative supplemental oxygen, especially on the cardiovascular system, still remains unknown. A post-hoc analysis of the PROXI trial indicated an increased long-term risk of myocardial infarction or other heart diseases in patients receiving supplemental oxygen [7]. Despite the current controversy regarding toxic effects of supplemental oxygen [8], there are also studies indicating the beneficial effects of higher oxygen concentrations specifically on the cardiovascular system. A decrease in heart rate and myocardial oxygen consumption as well as an increase in myocardial oxygen supply was shown previously [9–11].

For example, nocturnal oxygen therapy significantly reduced the brain natriuretic peptide (BNP) concentration and prevented the progression of congestive heart failure in patients with central sleep apnea [12].

*N*-terminal pro-B-type natriuretic peptide (NT-proBNP) is a hormone, which is released during increased myocardial stress [13]. Measurement of NT-proBNP is recommended to enhance perioperative cardiac risk estimation in patients aged over 65 years of age or older, and also those aged 45–64 years of age with significant cardiovascular disease undergoing noncardiac surgery [14].

The preoperative assessment of NT-proBNP is recommended for patients at high risk of cardiovascular events undergoing noncardiac surgery [15]. Postoperatively elevated NT-proBNP concentrations are associated with increased postoperative cardiac mortality and cardiac failure within 30 days after noncardiac surgery [16].

No data are available regarding the effect of supplemental oxygen on postoperative NT-proBNP concentrations. Thus, we will test our hypothesis that perioperative supplemental oxygen (80% versus 30%) decreases the postoperative maximum NT-proBNP concentration assessed within 2 h, on postoperative day (POD) 1 and POD 3 in patients with increased cardiovascular risk factors undergoing moderate- to high-risk noncardiac surgery. Furthermore, we will evaluate differences of NT-proBNP concentration within 72 h before discharge between both study groups. Our secondary outcomes will test the effect of supplemental oxygen on postoperative troponin T (TnT) concentration, oxidation-reduction potential and von Willebrand factor (vWF) concentration and perioperative fluid requirements.

## Methods/design: data collection, management and analysis

### Objectives and design

We will conduct a single-center, double-blinded, two-arm trial at the Medical University of Vienna. In total, we will randomly assign 260 patients to receive 80% versus 30% inspired oxygen concentration for surgery and for 2 h postoperatively. We will follow the Standard Protocol Items: Recommendations for Interventional Trials (SPIRIT) recommendations for interventional trials (Additional file 1). The study was approved by the Ethics Committee of the Medical University of Vienna on 13 November 2017. This trial was registered at ClinicalTrials.gov on 8 December 2017 (NCT03388957) and at the European Clinical Trial Database (2017–003714-68).

This trial will test the primary hypothesis that supplemental oxygen significantly decreases the maximal postoperative NT-proBNP concentration (assessed within 2 h after surgery, on POD 1 and POD 3) in patients with increased cardiovascular risk factors undergoing moderate- to high-risk abdominal surgery.

Our secondary outcomes are differences in maximum TnT concentration, static oxidation-reduction potential (sORP) and oxidation-reduction potential capacity (cORP), as well as vWF values and the perioperative fluid requirements to reach hemodynamic stability (Table 1).

**Table 1 Tab1:** Outcomes assessment

	Outcomes	Measurements
Primary	Myocardial function	maxNT-proBNP
Secondary	MINS	maxTnT
	Surgical stress	Copeptin
	Redox stress	sORP, cORP
	Hemodynamic	
Exploratory	Cardiac failure	50% increase in NT-proBNP
	Myocardial infarction	ECG change and elevated heart-specific enzymes
	Heart failure requiring intervention	50% NT-proBNP increase and medical treatment
	New onset of cardiac arrhythmias	ECG changes requiring medical treatment and/or electric cardioversion
	Unplanned ICU admission	

c*ORP* oxidation-reduction capacity, *ECG* electrocardiogram, *ICU* intensive care unit, *maxNT-proBNP* maximal *N*-terminal pro-B-type natriuretic peptide, *maxTnT* maximal troponin T, *MINS* Myocardial Injury after Noncardiac Surgery, *sORP* static oxidation-reduction potential

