#### Follow-up

Patients will be followed up for the primary and secondary outcome within 2 h after surgery, on POD 1, POD 3 and within 3 days before discharge. Laboratory measurements for outcome assessments are shown in Table 1. We will further perform a telephone follow-up on the 30th day after surgery to evaluate cardiac events including acute heart failure, myocardial infarction and new onset of atrial fibrillation (Table 2). All follow-up measurements will be performed by an investigator who will be unaware of the randomized allocation. Acute heart failure will be defined as cardiac failure needing medical intervention including therapy with inotropes and extracorporeal membrane oxygenation. Myocardial infarction will be diagnosed according the fourth definition of myocardial infarction [21]. Atrial fibrillation will be diagnosed according to the management guidelines for atrial fibrillation [22].

**Table 2 Tab2:** Schedule of study events

Timepoints		Study period						
	Enrollment	Intervention			Postoperative period			Close out
	Preoperative visit	Before anesthesia	During surgery	End of surgery for 2 h after surgery	POD 1	POD 3	Hospital discharge	POD telephone follow-up

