#### Data analysis

Randomized groups will be compared for balance in patient characteristics, demographic data, type of surgery, duration of surgery and anesthesia and preoperative baseline laboratory values (including: NT-proBNP, TnT, hemoglobin, hematocrit, leukocytes, thrombocytes, prothrombin time, activated prothrombin time, sodium, potassium, calcium, magnesium, creatinine, albumin, transaminases, C-reactive protein). The primary analysis will be intention to treat so that all randomized patients will be included in all analyses.

The primary outcome, the effect of 80% versus 30% oxygen on postoperative maxNT-proBNP will be compared using a two-sample, two-tailed Mann-Whitney *U* test. If a patient dies before NT-proBNP on POD 3 is measured, the patient’s maxNT-proBNP will be set to the maximum maxNT-proBNP values over all patients. Multiple imputation will be used for missing postoperative measurements.

Our secondary outcomes including Myocardial Injury after Noncardiac Surgery (MINS) (defined as absolute change of high-sensitive TnT of 5 ng/L between 20 to < 65 ng/L) [23], surgical stress, redox stress and perioperative hemodynamic (fluid and vasopressor requirements) will be analyzed using a two-sample, two-tailed Mann-Whitney *U* test. The exploratory outcomes including cardiac failure, myocardial infarction, acute heart failure requiring intervention, new onset of cardiac arrhythmias and unplanned ICU admission will be analyzed using Kaplan-Meier curves assessed with a log-rank test (Table 1).

If hospital discharge occurs before the third POD, the maximum value of the available data will be used for outcome measure.

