#### Sample size consideration

A previous study showed a nearly 40% reduction of BNP levels in patients with congestive heart failure receiving nocturnal oxygen therapy [12]. Based on our own data of a previous trial (unpublished data) we observed a fourfold increase of BNP (preoperative 129.05 ng/L ± 160.13 to up to 482.49 ng/L ± 538.78) in the postoperative period in relatively healthy patients undergoing moderate- to high-risk open abdominal surgery. We calculated a needed sample size of 254 patients (127 patients per group) to show a 40% reduction of NT-proBNP in patients receiving 80% versus 30% oxygen with a power of 80% at a 0.05 significance level. We will thus include 260 patients (130 patients per group) to compensate for potential drop outs.

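### Table 1 defines the exploratory outcome 'Cardiac failure' only as a 50% NT-proBNP rise, well below the roughly fourfold rise in the plan's own surgical data

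*Protocol article*

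**What the plan says.** Objectives and design, Table 1, lists two related exploratory rows. 'Cardiac failure' is measured by "50% increase in NT-proBNP" and nothing else. 'Heart failure requiring intervention' is measured by "50% NT-proBNP increase and medical treatment". Neither row states the reference value for the 50%; the preoperative sample is the natural reading.

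Follow-up gives a clinical definition without a marker threshold: "Acute heart failure will be defined as cardiac failure needing medical intervention including therapy with inotropes and extracorporeal membrane oxygenation".

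Data analysis treats cardiac failure and acute heart failure requiring intervention as separate exploratory outcomes, which "will be analyzed using Kaplan-Meier curves assessed with a log-rank test". Adjudication of the trial outcomes lists acute heart failure for the blinded adjudicator but not cardiac failure. Reporting of serious adverse events names both terms among the events not handled as SAEs.

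The primary hypothesis uses the same marker: "supplemental oxygen significantly decreases the maximal postoperative NT-proBNP concentration (assessed within 2 h after surgery, on POD 1 and POD 3". Sample size consideration states that "we observed a fourfold increase of BNP" ("preoperative 129.05 ng/L ± 160.13 to up to 482.49 ng/L ± 538.78"), seen "in the postoperative period in relatively healthy patients undergoing moderate- to high-risk open abdominal surgery".

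**The concern.** A cut-off for cardiac failure should separate patients with the condition from those without it. Here the cut-off is 1.5 times the reference value, while the sponsor's own data show a mean rise of about 3.7 times in patients described as relatively healthy. The Discussion attributes such rises to the stress of surgery and anesthesia. Read literally, the rule labels the ordinary surgical response as cardiac failure.

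Two things are at stake. First, the trial would report a cardiac failure rate covering most control patients, against a rate of major cardiovascular complications of about 3% cited in the Background. Second, the outcome is built from the primary marker, so any effect of oxygen on NT-proBNP would also appear as fewer cardiac failures without independent clinical information.

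The terms also do not line up across sections. Heart failure needing treatment requires a marker rise in Table 1 but not in Follow-up, and the marker-only outcome falls outside the list of adjudicated events.

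**Working it through.** **Inputs from the protocol article.** Preoperative mean 129.05, SD 160.13 ng/L; postoperative mean 482.49, SD 538.78 ng/L; planned reduction 40%; power 80%; alpha 0.05, two-tailed (Sample size consideration, Data analysis). Threshold ratio 1.5 (Table 1).

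**Assumed.** The 50% is measured from the preoperative value. Pre and post values are log-normal. The within-patient correlation r of log values is unknown and is varied from 0 to 0.9.

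**Step 1: are the planning figures usable?** Difference = 0.40 × 482.49 = 193.0; standardised effect = 193.0/538.78 = 0.358. A two-sample t-test needs 124 per group (248 in total). Dividing by 0.955 for the Mann-Whitney test gives 129–130 per group (258–260). The stated 254 (127 per group) lies between, and power at 127 per group is about 81%. The stated sample size is reproduced, so the same figures can be used for the threshold.

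**Step 2: typical rise.** Ratio of means = 482.49/129.05 = 3.74, an increase of 274%. After a 40% reduction, 0.6 × 3.74 = 2.24. Matching log-normals by variance = ln(1 + (SD/mean)²) and median = mean × exp(−variance/2):
- preoperative: log SD 0.965, median 81 ng/L
- postoperative: log SD 0.900, median 322 ng/L
- ratio of medians 3.97, natural log 1.380

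**Step 3: share above +50%.** The SD of the log ratio is s = √(0.965² + 0.900² − 2r × 0.965 × 0.900). The share is Φ[(ln(F) − ln(1.5))/s], where F is the median fold rise: 3.97 in controls and 0.6 × 3.97 in treated patients under the full planned effect.

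| r | s | Controls | Treated, 40% reduction | Difference (points) |
|---|---|---|---|---|
| 0 | 1.320 | 77% | 64% | 13 |
| 0.3 | 1.105 | 81% | 66% | 15 |
| 0.5 | 0.934 | 85% | 69% | 16 |
| 0.7 | 0.725 | 91% | 74% | 17 |
| 0.8 | 0.593 | 95% | 78% | 17 |
| 0.9 | 0.422 | 99% | 86% | 13 |

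Example, r = 0.5, controls: (1.380 − 0.405)/0.934 = 1.04, and Φ(1.04) = 0.85.

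**Step 4: smaller relative rise.** The trial enrols higher-risk patients, whose baseline may be higher and relative rise smaller. Take a median rise of twofold in controls (assumed), so 0.6 × 2 = 1.2-fold in treated patients, with the same s.
- Controls: (ln 2 − ln 1.5)/s = 0.288/s, giving 59% at r = 0 and 75% at r = 0.9.
- Treated: (ln 1.2 − ln 1.5)/s = −0.223/s, giving 43% at r = 0 and 30% at r = 0.9.

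Under this model fewer than half of controls qualify only if their median rise is below 1.5-fold.

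**Step 5: definitions side by side.**

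| Section | Term | Marker threshold | Treatment |
|---|---|---|---|
| Table 1 | Cardiac failure | 50% rise | none |
| Table 1 | Heart failure requiring intervention | 50% rise | medical treatment, unspecified |
| Follow-up | Acute heart failure | none | medical intervention, with examples |
| Adjudication | Acute heart failure only | – | – |

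A patient treated for heart failure without a 50% rise meets the Follow-up definition and fails Table 1.

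**Step 6: timing.** NT-proBNP is sampled preoperatively, within 2 h after surgery, on POD 1, on POD 3 and within 3 days of discharge. The day-30 contact is by telephone and cannot detect a marker rise. Event times are therefore sampling times, and the last one depends on length of stay.

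**The case against.** The strongest reply has five parts.

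- **Population.** The planning data are labelled BNP and come from relatively healthy patients, whereas eligibility requires established vascular disease or several risk factors. The Discussion itself says data in such patients are lacking. This stands. With a twofold rise, a majority qualifies among controls but not among treated patients, so the 77–99% range is no forecast.
- **Not the primary in disguise.** A reader might infer that this outcome is just the primary endpoint dichotomised. The documents do not support that. The primary is the absolute postoperative maximum; this is a relative change. A patient with a high baseline can have a high maximum and no 50% rise. What remains is that the marker and most samples are shared.
- **Treatment wording.** A reader might also infer that Table 1 and Follow-up contradict each other on treatment. They need not, because the Follow-up list is open-ended and Table 1's general term fits within it. The real difference is the marker threshold.
- **Existing safeguards.** Acute heart failure is already adjudicated blind, and the adjudicator's decisions are used in the analysis. This stands and confines the adjudication gap to the separate cardiac failure row.
- **Kaplan-Meier.** To say the method cannot observe the event would go too far. The samples at 2 h, POD 1 and POD 3 are common to both arms, and discharge can be a censoring time. The method is poorly suited, not impossible.

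The row is also exploratory, its measurement is printed beside its label, and the protocol announces no clinical claim from it.

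**Conclusion.** The point holds as one of labelling and consistency. The 50% rule for 'Cardiac failure' sits far below the average rise in the plan's own data, so it mostly records the expected surgical marker response. The control-arm majority persists at every correlation tried, with either the planning rise or a twofold rise. In the treated arm it persists with the planning rise (64–86%) but not with the twofold rise (30–43%). All these shares rest on log-normality, an unknown correlation, a preoperative reference and, for the second set, an assumed fold rise.

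With the planning rise, the full planned 40% reduction would by itself show as a drop of about 13–17 percentage points in this outcome. The definitional mismatch is real but narrow: the marker threshold that Follow-up lacks, and the absence of cardiac failure from the adjudication list. Nothing here affects the primary comparison, the secondary outcomes or the sample size.

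**What to change.** 1. In Table 1 and Data analysis, relabel the 50% rise as a biomarker response, state its reference value, and do not report it as cardiac failure. Dropping the row is the alternative.
2. Reconcile Table 1, Follow-up, Data analysis, Adjudication of the trial outcomes and Reporting of serious adverse events so that heart failure has one definition and one name and is adjudicated blind. Whether a marker threshold belongs in it is for the investigators to decide; it should be the same everywhere.
3. If the 50% rise is kept, analyse it as the proportion of patients meeting it by POD 3, with a risk difference and confidence interval, in place of Kaplan-Meier and log-rank.

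**Cost.** Edits to the outcome table and analysis plan, and one fewer, or a less dramatic, clinical event rate to report. No new data are needed, which matters because Trial status says recruitment is complete.

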### Study population

We will screen for patients of at least 45 years of age planned for elective moderate- to high-risk abdominal surgery under general anesthesia with an expected duration of surgery of at least 2 h. Patients are eligible if they meet one or more the following criteria: (1) history of coronary artery disease; (2) history of peripheral arterial disease; (3) history of stroke o*r* (4) any three of these six criteria: (a) age over 70 years, (b) undergoing major surgery, (c) history of congestive heart failure, (d) history of transient ischemic attack, (e) diabetes and currently taking an orally administered hypoglycemic agent or insulin and (f) history of hypertension. Patients will be not eligible if they meet one of the following criteria: (1) symptoms of infection or sepsis; (2) preoperative inotropic therapy; (3) patients under intensive care unit (ICU) treatment; (4) oxygen-dependent patients and (5) history of severe heart failure and/or an ejection fraction < 30%. (Fig. 1).

**Fig. 1 Fig1:**
[figure not shown]
Study flow chart. *BNP* brain natriuretic peptide, *TnT* troponin T, *sORP* static oxidation-reduction potential, *cORP* oxidation-reduction potential capacity, *POD* postoperative day

### Protocol

We will perform standardized monitoring including electrocardiogram (ECG), blood pressure and oxygen saturation (SpO_2_) in all patients after arriving in the operating theater. Shortly before induction of anesthesia, patients will be randomly assigned to one of the two oxygen concentrations. We will administer 100% oxygen in all patients for induction of anesthesia according to clinical standards. We will induce anesthesia using 1–3 μg kg^− 1^ body weight (BW) fentanyl, 2 mg kg^− 1^ (BW) propofol and 0.6 mg kg^− 1^ rocuronium. In addition to standard monitoring, an arterial line will be inserted for direct blood pressure monitoring. A central venous line will be inserted at the discretion of the attending anesthesiologist.

Anesthesia will be maintained with sevoflurane (up to 1.5 minimum alveolar concentration (MAC)) in an oxygen gas carrier according to processed electroencephalogram (EEG)-guided anesthesia. Muscle relaxation will be given when necessary to maintain one to two mechanical twitches in response to supra-maximal stimulation (Train-of-Four stimulation, target < 75%). Temperature will be held at a core temperature over 36 °C using forced-air warming.

We will use esophageal-Doppler-guided (Cardiac Q, Deltex Medical, Chichester, UK) fluid management according to a previously published algorithm [17, 18]. All patients will receive a 2 mL/kg BW baseline infusion of balanced crystalloids. A bolus of 250 mL balanced crystalloids will be administered when the stroke volume decreases by more than 20% as compared to baseline values. In the case of acute bleeding or a systemic inflammatory response during surgery, volume will be administered according to fluid requirements to maintain hemodynamic stability. Blood and blood products will be administered per clinical judgment.

There will be no restrictions or prohibitions of medical care and therapeutics during hospital stay in case of enrollment.

### Intervention

After endotracheal intubation we will set the inspired oxygen fraction according to randomization. Patients randomly assigned to the 80% oxygen group will receive an inspired oxygen fraction of 0.8 after intubation; those randomly assigned to the 30% oxygen will receive an inspired oxygen fraction of 0.3 in air. Patients will be blinded to group allocation.

We will use 80% versus 30% oxygen concentration to receive the maximum difference between oxygen concentrations without the risk of causing damage, e.g., increased formation of atelectasis [19]. Moreover, almost all studies investigating the effect of supplemental oxygen on, for example, postoperative wound infection used 80% versus 30% inspired oxygen concentration during surgery [5, 6, 20].

Maintaining a minimum SpO_2_ of at least 93% will be attempted. In the case of SpO_2_ < 93% the following interventions to improve oxygenation will be performed: (1) positive end-expiratory pressure (PEEP) will be increased incrementally by 2 cmH_2_O up to maximally 12 cmH_2_O; (2) recruitment maneuver: the inspiratory pressure will be set at 55 cmH_2_O. The PEEP will be set at 12 cmH_2_O and respiratory rate to six breaths/min or higher. Inspiratory pressure will be set to receive a tidal volume of 6 mL/kg ideal BW. The inspiratory ratio will be set (I:E) to 1:1. Inspiratory pressure will be increased until a plateau pressure reaches 40–50 cmH_2_O. After allowing three breaths while maintaining a plateau pressure of 40–50 cmH_2_O, the respiratory rate and inspiratory pressure will be set back to pre-recruitment parameters and (3) if both interventions are not sufficient to increase SpO_2_, then the inspiratory oxygen fraction will be elevated by 0.1 until 93% SpO_2_ is reached.

